## Methods

### Objectives

#### Primary objective:

To identify a combination of biomarkers that distinguishes patients with transmural AMI from patients with no AMI with a positive likelihood ratio of > 10 and negative likelihood ratio of < 0.1 at least at one measurement time point before any treatment of AMI (comparison A).

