#### Blood sampling time points

Two sampling tubes (one serum and one plasma, arterial or venous) will be collected at each measurement point, allowing central measurement of aforementioned biomarkers.

Depending on whether AMI is confirmed or not, and on treatment methods applied, different measurement time points will apply for each patient (Table 1 and Fig. 1).

**Table 1 Tab1:** Sampling time points for biomarkers measurements (M)

M no	Time point for blood sampling	Confirmed AMI with intervention	Suspicion of AMI*	Confirmed AMI without intervention
M1	Admission (suspicion, if in-hospital)	x	x	x
M2	6-8 h after the first sample if no intervention performed by then	x (if no intervention before 6-8 h)	x	x
M3	At intervention	x (incl. i/a vasodilation)		
M4	4–6 h after intervention	x		
M5	12 h after intervention	x		
M6	24 h after the first sample if no intervention		x (if suspicion still actual)	x
M7	At the time of re-intervention	x (if any within 72 h)		
M8	48 h after the first sample		x (if suspicion still actual)	x (if no intervention)

* If the case is confirmed, the patient will be moved to either column “Confirmed AMI with intervention” or “Confirmed AMI without intervention”

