Statistical analysis will be performed with R Statistical Software 4.3.2 (R Core Team, Vienna, Austria, 2023). Data will be described in number (%), median (interquartile range, IQR) or mean (standard deviation, SD) as appropriate. Kolmogorov–Smirnov test will be used for data distribution normality testing. Analyses for confirmed transmural AMI vs suspected but not confirmed AMI (comparison A – primary outcome), confirmed AMI of any stage vs suspected but not confirmed AMI (comparison B – secondary outcome) and transmural vs non-transmural AMI (comparison C – secondary outcome) will be performed in different measurement time points. Each biomarker will be described at each measurement point for all comparisons (A, B and C), using Student’s t-test or Wilcoxon rank-sum test as appropriate. For all biomarkers showing a *p*-value < 0.05 in at least one measurement point in univariate analysis, the area under the receiver operating curve (ROC) calculation will be performed. We will do this separately for comparisons A, B and C and identify optimal cut-off values for each biomarker based on maximum value of the Youden index [13]. All measurement time points before any treatment of AMI (1,2,3,6,8) will be pooled and AUROC analysis will be performed to identify the best cut-offs also for pooled data for each biomarker. Sensitivity, specificity, positive predictive value (PPV), negative predictive value (NPV) and likelihood ratios (LR) with 95% CI-s will be reported. Positive likelihood ratio (LR +) > 10 and negative likelihood ratio (LR-) < 0.1 will be considered high diagnostic accuracy and LR +  > 5 and LR- < 0.2 as moderate diagnostic accuracy. All biomarkers with at least moderate accuracy will be entered as binary covariates (using the best cut-offs previously found in the AUROC analyses resulting in highest AUC) into the multivariable stepwise logistic regression analysis (both directions) to identify the best combination of biomarkers discriminating between transmural AMI and no AMI based on Akaike information criterion (AIC). Analogical approach will be used for comparisons B and C. The best models will be applied to subgroup analyses in different sub-types of AMI. If the best models selected as described previously, do not perform well at different measurement time points or in different subtypes of AMI, additional analyses will be undertaken testing alternative combinations. We will present the best models for each comparison and for each subtype separately and will use them to construct a practical score that can be used to distinguish between no AMI, non-transmural AMI and transmural AMI (Table 3). If the different cut-offs from different models contradict (for example cut-off for non-transmural AMI vs transmural AMI is lower than the cutoff for no AMI vs AMI) additional analyses will be performed and more appropriate cut-offs will be found considering acceptable sensitivity and specificity from previous AUROC analyses. This approach will be compared to decision tree approach and if the decision tree accuracy is higher than the score’s accuracy, a decision tree will be preferred. The accuracy of the decision tree and the score will be calculated as proportion of correct predictions.

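### The marker screen and cut-off choice are not limited to pre-treatment samples, so comparison C can be built on post-treatment data, and A and B are given tests for which Table 1 supplies no controls

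*Protocol article*

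**What the plan says.** The primary objective asks for discrimination "at least at one measurement time point before any treatment of AMI (comparison A"). The two secondary objectives, for B and C, carry the same pre-treatment limit. Post-treatment samples appear only under the tertiary objectives, which describe marker patterns before and after treatment.

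The analysis paragraph that follows the sample size text sets this sequence:

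- Testing: "Each biomarker will be described at each measurement point for all comparisons (A, B and C), using Student’s t-test or Wilcoxon rank-sum test as appropriate".
- Screen: a marker goes on to ROC analysis if p < 0.05 "in at least one measurement point in univariate analysis".
- Cut-offs: the Youden index is used separately for A, B and C. In addition, "All measurement time points before any treatment of AMI (1,2,3,6,8) will be pooled" for a further AUROC analysis, "to identify the best cut-offs also for pooled data for each biomarker".
- Entry to the model: markers with at least moderate accuracy (LR+ > 5 and LR- < 0.2) enter as binary covariates, "using the best cut-offs previously found in the AUROC analyses resulting in highest AUC".

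Table 1 (Blood sampling time points) marks M3 (at intervention), M4 ("4–6 h after intervention"), M5 (12 h after it) and M7 (at re-intervention) only for confirmed AMI with intervention. Patients with unconfirmed suspicion are sampled at M1 and M2 and, while the suspicion persists, at M6 and M8.

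**The concern.** The list of pre-treatment points governs only the pooled AUROC, and the word 'also' places that analysis beside the per-point ones. The screen, the per-point ROC analyses and the highest-AUC rule carry no time limit. Read as written, they can select on samples that the objectives exclude.

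This matters because the score is meant to guide a decision taken before treatment. The Background section says the transmural assessment matters for choosing between endovascular and open surgical treatment. The protocol also expects levels to change once blood flow returns: Table 2 cites animal data in which D-lactate and IL-6 rise with reperfusion, and SCUBE-1 slightly. A cut-off learned at M4, M5 or M7 may therefore not carry over to M1.

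For A and B there is a different mismatch. The plan prescribes comparisons at points where the sampling table provides only one of the two groups.

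**Working it through.** **Step 1. The plan's own list.** Removing the points that follow an intervention (M4, M5, M7) from M1 to M8 leaves {1, 2, 3, 6, 8}. This reproduces the list given for the pooled analysis.

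**Step 2. Points at which each comparison can be made (Table 1).**
- Cases: M1 to M8. Unconfirmed patients: M1, M2, M6, M8.
- A and B: both groups exist only at {M1, M2, M6, M8}. Four of the eight prescribed tests (M3, M4, M5, M7) have no control group. All four usable points are pre-treatment.
- C: both groups are cases, so all eight points are usable. Three of them (M4, M5, M7) lie outside the objective.

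**Step 3. Can the likelihood-ratio requirement be met on post-treatment samples?** The means are assumptions, with normal distributions and SD 1; the documents give none. With equal SDs the Youden cut-off is the midpoint of the two means.
- Post-treatment, 0.5 vs 2.5, cut-off 1.5: sensitivity = specificity = Φ(1) = 0.841. LR+ = 0.841/0.159 = 5.3 and LR- = 0.159/0.841 = 0.19. Both meet the moderate level. AUC = Φ(2/√2) = 0.92.
- Pre-treatment, 0 vs 1, cut-off 0.5: sensitivity = specificity = Φ(0.5) = 0.691. LR+ = 0.691/0.309 = 2.2 and LR- = 0.309/0.691 = 0.45. Both fail. AUC = Φ(1/√2) = 0.76.
- Post-treatment cut-off 1.5 applied before treatment: sensitivity = 1 - Φ(0.5) = 0.309 and specificity = Φ(1.5) = 0.933. LR+ = 0.309/0.067 = 4.6 and LR- = 0.691/0.933 = 0.74. Both miss the moderate level.

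Under these assumptions the highest-AUC rule prefers the post-treatment point. The marker enters the model for C on data outside the objective, although on pre-treatment data it would be rejected.

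**Step 4. How often would the highest AUC fall after treatment in C?** If all eight points were equally informative and independent, the chance is 3/8 = 37.5%. A simulation with 60 vs 60 patients at every point (assumed) gave about 37%. With assumed AUCs of 0.65 before and 0.75 after treatment it gave about 96%.

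**Step 5. M3 in the A/B pool.** Take a marker with no true case-control difference at any shared time point, but which rises by d SD by M3. Let f be the share of case samples that come from M3 (d and f are assumptions). The pooled AUC is (1 - f) × 0.5 + f × Φ(d/√2).
- d = 0.5, where Φ(0.354) = 0.638: f = 0.2 gives 0.53 and f = 0.4 gives 0.56.
- d = 1, where Φ(0.707) = 0.760: f = 0.2 gives 0.55 and f = 0.4 gives 0.60.

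The shift is modest, but it comes only from adding M3 samples to one group.

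**The case against.** - **Reach.** A reader might infer that post-treatment cut-offs threaten all three objectives, including the primary one. Table 1 rules that out: without controls at M4, M5 and M7, no A or B test or AUROC can be computed there. This part of the objection stands in full.
- **Reading.** The highest-AUC phrase names no time point. With pre-treatment objectives and the pooled list nearby, it could be meant to cover pre-treatment data only, and describing markers at every point also serves the tertiary aim. That reading is possible for the cut-off but is not written. It does not help the screen, whose scope is explicit.
- **Later safeguards.** The plan will test alternative combinations if the best models do poorly at some time points, and will revise contradictory cut-offs. The objectives are judged before treatment, so a badly transferred cut-off would tend to miss the target rather than falsely meet it. That is fair, and it lowers the stakes. But these steps come after selection, and the article attaches no criterion to them.
- **Multiplicity.** A reader might cite the chance that a null marker passes the screen for C at some point, 1 - 0.95^8 = 34% with independent points, as the size of this problem. Most of that remains after the fix: 1 - 0.95^5 = 22.6%. At a correlation of 0.9 between points the change is only from 12.0% to 10.1%. For A and B it is 18.5% (independent points) before and after.
- **Assumed means.** The illustration in Step 3 shows what the rule permits. It does not predict what will happen.

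**Conclusion.** The point holds, with limited reach. As written, the screen, the per-point ROC analyses and the cut-off choice may use samples that the objectives exclude.

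The selection error can occur only in secondary comparison C, where three of eight candidate points are post-treatment. The likelihood-ratio requirement is no protection, since it can be satisfied on the same samples that supplied the cut-off. How large the effect would be depends on how far the markers shift after treatment, which the documents do not quantify.

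For A and B the defect is different and smaller. Four of eight prescribed tests have no comparator, and M3, which is pre-treatment by the plan's own list, enters the pool from cases only. This follows Table 1 as designed; the article does not say whether a patient sampled at an intervention and later not confirmed would count as a control.

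A reader might also conclude that the cut-off should come from one fixed time point. The documents do not support that: the objectives accept success at any one pre-treatment point, and the Background expects the best combination to vary with time.

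**What to change.** In the Statistical analysis section, state that the univariate screen, the per-point ROC analyses and the choice of cut-off use only pre-treatment points at which both groups are sampled:

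- A and B: M1, M2, M6 and M8.
- C: M1, M2, M3, M6 and M8.

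Drop M3 from the pooled analysis for A and B. State that M4, M5 and M7 serve only the descriptive tertiary objective.

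The cost is analysis wording alone: no extra samples or patients, and C goes from eight candidate time points to five. If this was always the intention, the edit records it before the data are seen.

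### Pooling M1, M2, M3, M6 and M8 to find cut-offs mixes a sampling schedule that depends on diagnosis and clinical course, with no stated allowance for repeated samples per patient

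*Protocol article*

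**What the plan says.** In the protocol article, the Statistical analysis section first plans ROC analyses by time point for comparisons A (transmural against unconfirmed), B (any AMI against unconfirmed) and C (transmural against non-transmural). In these the plan is to "identify optimal cut-off values for each biomarker based on maximum value of the Youden index". It then adds: "All measurement time points before any treatment of AMI (1,2,3,6,8) will be pooled and AUROC analysis will be performed", in order "to identify the best cut-offs also for pooled data for each biomarker". Among the results, "likelihood ratios (LR) with 95% CI-s will be reported"; no interval method is named. Markers then enter the stepwise regression as binary covariates, "using the best cut-offs previously found in the AUROC analyses resulting in highest AUC".

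The section on blood sampling time points says that "different measurement time points will apply for each patient", depending on confirmation and treatment. In Table 1, M3 is marked only for confirmed AMI with intervention, "x (incl. i/a vasodilation"), and is blank in the other two columns. M6 and M8 in unconfirmed patients are marked "x (if suspicion still actual").

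**The concern.** Two things meet in the pooled analysis. First, each patient contributes several correlated values, so an interval that counts samples overstates precision. Second, the samples that represent each group are set by what happened to the patient. Cases with intervention are represented by M1 and M3, sometimes M2. Controls who are quickly cleared are represented by M1 and M2, and controls who remain in doubt also by M6 and M8. Time since admission and persisting suspicion are therefore mixed with disease status.

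This sits badly with the article's own reasoning. The Background criticises earlier work for measuring at differing periods after symptom onset and expects the best combination to depend on the time point. The Ethics section expects several markers to peak within 6 h. At stake is whether a cut-off that partly reflects sampling time is carried into the regression and the bedside score.

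**Working it through.** **Inputs from the article.** The target is 250 patients: 160 with confirmed AMI and 90 unconfirmed. The article gives no figure for the pooled analysis. Its recruitment count can be roughly reproduced: 20 × 14 × 0.8 = 224 (stated 220), 20 × 7 × 0.8 = 112 (stated 120), and 340 × 0.95 × 0.90 × 0.85 = 247 against 250. Nothing below depends on that count beyond the 160 and 90.

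**Who enters the pool, from Table 1:**

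| Group | M1 | M2 | M3 | M6 | M8 | Samples |
|---|---|---|---|---|---|---|
| AMI with intervention | yes | only if no intervention before 6-8 h | yes | no | no | 2-3 |
| AMI without intervention | yes | yes | no | yes | yes | up to 4 |
| Unconfirmed | yes | yes | no | while suspicion lasts | while suspicion lasts | 2-4 |

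A patient confirmed late changes column (table footnote), so five is possible. Only M1 is free of status-dependence. At M3, comparisons A and B have no control group.

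**Assumptions not in the article.** Within-patient correlation (ICC) is 0 to 0.9. Of AMI patients, 70-90% have an intervention. Of unconfirmed patients, 30-50% are still suspected at 24 h. Time trends run from -1 to +1 SD per 24 h, and the AUC at M1 is about 0.86. At 70% intervention, with half of those patients giving an M2, cases give 112 × 2 + 56 + 48 × 4 = 472 samples. Controls give 180 + 72 = 252, the 72 being M6 and M8. The total is 724, or 724/250 = 2.9 per patient.

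**Interval width, by formula.** SE ratio (correct/naive) = √(1 + (m − 1) × ICC), and coverage = 2Φ(1.96/ratio) − 1.

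| m | SE ratio, ICC 0.3 to 0.9 | Coverage of nominal 95% |
|---|---|---|
| 2 | 1.14 to 1.38 | 91% to 85% |
| 3 | 1.26 to 1.67 | 88% to 76% |
| 4 | 1.38 to 1.92 | 85% to 69% |

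**Interval width, by simulation** of the Table 1 schedule with stationary levels (300-600 runs per scenario, so coverage carries a Monte Carlo SE of about 1.5 to 2 percentage points):

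| ICC | True/naive SE of pooled AUC | Coverage, AUC | Coverage, specificity | Coverage, sensitivity |
|---|---|---|---|---|
| 0 | 1.05 | 94% | 93% | 94% |
| 0.3 | 1.25 | 88% | 90% | 89% |
| 0.5 | 1.34 | 86% | 86% | 88% |
| 0.7 | 1.48 | 82% | 85% | 82% |
| 0.9 | 1.57 | 81% | 82% | 81% |

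**Cut-off shift.** The Youden cut-off, pooled minus M1, in SD units at ICC 0.5; the two figures are for 70% and 90% intervention:

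- No trend: 0.745 − 0.739 = 0.01; 0.740 − 0.716 = 0.02, within simulation noise.
- Cases rise 1 SD per 24 h: 0.915 − 0.722 = 0.19; 0.883 − 0.730 = 0.15.
- Cases and controls both rise: 1.043 − 0.729 = 0.31; 1.016 − 0.724 = 0.29.
- Cases fall: 0.605 − 0.714 = −0.11; 0.631 − 0.719 = −0.09.
- No trend, but controls with high values resampled more often: 0.79 − 0.73 = 0.06 at ICC 0.5; 0.82 − 0.73 = 0.09 at ICC 0.7.

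Dropping M3 alone moves the pooled cut-off by at most 0.883 − 0.844 = 0.04 SD, and the AUC by at most 0.814 − 0.801 = 0.013.

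**Can a pooled cut-off win on AUC?** When cases rise over time, the pooled AUC (0.90) exceeds that at M1 (0.86). When cases fall, it does not (0.78 against 0.86). Selection on AUC can therefore favour the pool because of the trend. Single late time points were not compared here.

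**Predictive values.** For comparison B the share of cases is 160/250 = 0.64 by patient, but 0.65-0.68 by sample. At the article's moderate-accuracy limits (LR+ 5, LR− 0.2), a share of 0.64 gives PPV odds of 1.778 × 5 = 8.89, so PPV 0.90, and NPV odds of 0.5625 × 5 = 2.81, so NPV 0.74. At 0.68, PPV odds are 2.125 × 5 = 10.6 (PPV 0.91) and NPV odds 0.471 × 5 = 2.35 (NPV 0.70).

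**The case against.** A reader might infer that the plan analyses samples as independent. The article does not say so. It is silent on the interval method, and a clustered variance or patient-level bootstrap could stand in an analysis plan not shown here. That stands, and the coverage figures describe only what ordinary intervals would do. No variance method, however, changes which samples represent which group, and that mix is fixed by the text.

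A reader might also infer that the case-only M3 samples bias the cut-offs. They need not. Sensitivity, specificity and the Youden index do not depend on how many case samples there are. A shift needs time trends or informative resampling, and M3 is a minor driver compared with the schedule as a whole. The expected early peaks make trends plausible but do not fix their size or direction.

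The pooled analysis is additional, and the objectives ask for accuracy at one or more time points. The likelihood-ratio thresholds are not tied to interval limits, and regression selection uses AIC. Narrow intervals would therefore misstate precision without triggering any stated decision. All of this limits the consequence. What remains is the highest-AUC rule, by which a pooled cut-off can, though need not, reach the score.

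Finally, it is tempting to say that the late samples of confirmed patients without intervention are not truly pre-treatment. The article does not say what else those patients receive. It shows only that the pool is defined by treatment while Table 1 is organised by intervention.

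**Conclusion.** The point holds in a conditional form and should be fixed; it does not undermine the study. Fixed by the text are the pooling, the status-dependent schedule and the route by which a pooled cut-off can enter the model. Conditional on assumed values are coverage of about 81-88% for ordinary intervals on the pooled AUC (ICC 0.3-0.9), a cut-off shift of about −0.1 to +0.3 SD under the assumed trends, and predictive values resting on a case share of 0.65-0.68 instead of 0.64. With stationary levels and uninformative resampling the cut-off shift is about zero. Restricting the pool to M1 and M2 would not give balance by design, because M2 also depends on early intervention.

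**What to change.** - Keep the pooled analysis secondary, and state that its cut-offs do not compete on AUC for entry into the regression.
- Take model cut-offs from analyses at a single time point, one sample per patient and both groups present, with M1 as the main one. Other time points remain available, which respects the serial design; making M1 the only source would be a trade-off against it.
- In any pooled analysis, leave M3 out of comparisons A and B, weight patients equally, account for time point, and compute intervals by a bootstrap that resamples patients.
- State that M2, M6 and M8 also depend on status and course. In comparison C, note that M3 depends on who receives an intervention.
- Reconcile the pre-treatment label in the Statistical analysis section with the intervention-based columns of Table 1.

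This is a change of analysis wording and needs no new data. The cost is wider intervals, and some late samples become descriptive. It should be settled before cut-offs are derived.

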### Statistical analysis

#### Sample size

The estimated sample size is in total of 250 patients, 160 patients with confirmed AMI (including 40 patients with NOMI) and 90 patients with suspected but not confirmed AMI.

In the AMESI study, European and West-Asian sites recruited 14 patients with confirmed AMI in average (range 3–34) and 7 (range 0–25) with suspected but eventually not confirmed AMI per site during 10 months. Accordingly, 20 sites are expected to encounter 220 patients with confirmed AMI and 120 patients with suspected AMI during 8 months. Estimating 5% of patients allocated to palliative treatment without any further diagnostics, 10% of referrals and 15% of patients being excluded for other reasons (e.g. missing informed consent, logistical reasons), 20 sites recruiting patients during 8–10 months are necessary to reach the targeted number of patients. As the number of patients with suspected AMI and confirmed NOMI is difficult to predict, the final decision regarding recruitment period will be made after the interim analysis after 4 months of the study.

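### Comparison A leaves out non-transmural AMI, so a PPV computed within it overstates the PPV for transmural AMI among patients with suspected AMI

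*Protocol article*

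**What the plan says.** The Statistical analysis section of the protocol article defines three comparisons:

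- A: "Analyses for confirmed transmural AMI vs suspected but not confirmed AMI (comparison A – primary outcome". Non-transmural AMI is in neither group.
- B: "confirmed AMI of any stage vs suspected but not confirmed AMI (comparison B – secondary outcome". No class is left out.
- C: "transmural vs non-transmural AMI (comparison C – secondary outcome". Patients without AMI are in neither group.

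Of the ROC analysis and choice of cut-offs it says "We will do this separately for comparisons A, B and C". The list of accuracy measures follows: "Sensitivity, specificity, positive predictive value (PPV), negative predictive value (NPV) and likelihood ratios (LR) with 95% CI-s will be reported". No denominator for PPV and NPV is given, and no standardisation to a prevalence.

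The primary objective is a biomarker combination that "distinguishes patients with transmural AMI from patients with no AMI", with LR+ above 10 and LR- below 0.1. The planned sample is "160 patients with confirmed AMI (including 40 patients with NOMI) and 90 patients with suspected but not confirmed AMI". The split of the 160 into transmural and non-transmural is not given.

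The end product is a score for all three classes. Table 3 (hypothetical) attaches a PPV to each score band, also without a denominator.

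**The concern.** Sensitivity and specificity are computed within a class, so leaving out a third class does not change them. Predictive values depend on the mix of classes among the patients tested. Comparison A's mix cannot be formed prospectively. The first sample is taken at admission or at suspicion (Table 1), when nobody knows which patients will prove to have non-transmural AMI. Those patients will be tested too, and every one who tests positive is a false positive for transmural AMI that comparison A does not count.

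The design gives reason to expect such positives. The Youden cut-off for A is tuned against patients without AMI only, so nothing holds non-transmural patients below it. Table 3 sketches non-transmural disease at intermediate values for two of its five markers. Objective B hopes for combinations that are positive at any stage of AMI.

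At stake is the PPV reported for the primary comparison. If it is read as the chance that a suspected patient who tests positive has transmural AMI, it will be too favourable.

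**Working it through.** **The plan's own figures.** The article gives no PPV to reproduce. Its class sizes add up: 160 + 90 = 250. They also follow closely from the expected encounters if the stated losses are multiplied: 0.95 × 0.90 × 0.85 = 0.727, so 220 × 0.727 = 159.9 and 120 × 0.727 = 87.2.

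**Inputs from the protocol.** 160 confirmed AMI, 90 without AMI; LR+ 10 and LR- 0.1 as the limit for A.

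**Assumptions, not in the protocol.** The number of transmural patients T among the 160 (40, 80 or 120), with NT = 160 − T; and q, the share of non-transmural patients who test positive.

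**Sensitivity and specificity at the limit.** Sp = (LR+ − 1)/(LR+ − LR-) = 9/9.9 = 0.909. Se = LR+ × (1 − Sp) = 10 × 0.0909 = 0.909.

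**PPV.**

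- Within A: T·Se / [T·Se + 90(1 − Sp)]
- Over all 250: T·Se / [T·Se + 90(1 − Sp) + NT·q]

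With T = 80, true positives are 80 × 0.909 = 72.7 and false positives without AMI are 90 × 0.0909 = 8.2. Within A, PPV = 72.7/80.9 = 0.899. With q = 0.30, 24 further false positives enter and PPV = 72.7/104.9 = 0.693.

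| T / NT (assumed) | PPV within A | All 250, q = 0.09 | All 250, q = 0.30 | All 250, q = 0.50 |
|---|---|---|---|---|
| 40 / 120 | 0.816 | 0.656 | 0.451 | 0.348 |
| 80 / 80 | 0.899 | 0.825 | 0.693 | 0.602 |
| 120 / 40 | 0.930 | 0.902 | 0.844 | 0.795 |

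The two PPVs are equal only at q = 0. At the other end, if one combination at one cut-off just met the targets of both A and B, q would be about 0.91. With T = 80, PPV over all 250 would then be 72.7/(72.7 + 8.2 + 72.7) = 0.473.

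**NPV (T = 80, q = 0.30).** Within A: 81.8/(81.8 + 7.3) = 0.918. Over all 250, a negative result means not transmural with probability (81.8 + 56)/(81.8 + 56 + 7.3) = 0.950, and no AMI with probability 81.8/145.1 = 0.564. A's NPV is thus too low for one question and too high for the other.

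**LR+ as a test for transmural AMI in all suspected patients (T = 80, q = 0.30).** The false-positive rate among the 170 others is (8.2 + 24)/170 = 0.189, so LR+ = 0.909/0.189 = 4.8 rather than 10. Here the break-even is q = 1 − Sp = 0.09: above it the LR+ falls below 10, and below it the LR+ exceeds 10.

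**Comparison C, for contrast.** At LR+ 5 and LR- 0.2, Se = Sp = 4/4.8 = 0.833. With T = 80, PPV among confirmed AMI is 66.7/(66.7 + 13.3) = 0.833. It becomes 66.7/(80 + 15) = 0.702 only if the test is applied to all 250 and 17% of the 90 without AMI test positive.

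**The case against.** Four points can be made for the plan.

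1. No decision rests on these predictive values. The objectives, the accuracy grades and the entry of biomarkers into the model use likelihood ratios. Models are chosen by AIC, and score versus decision tree by the proportion of correct predictions. This stands. A reader might infer that the primary objective or the biomarker selection is compromised; the document does not support that, because A's likelihood ratios are correct for the contrast that A declares.

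2. The predictive values closest to the bedside are those of the Table 3 score, which separates all three classes and would most naturally be evaluated in all patients. This stands in part: the article does not give that denominator either, and pairwise PPV and NPV are still listed for reporting.

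3. The subset denominator is inferred, and a fuller plan may settle it. It is the natural reading of separate analyses for each comparison, but it is not written out. If all included patients are meant, a clarifying sentence is enough.

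4. A reader might infer that comparison C has the same defect, since it too leaves out a class. The document does not support this. Patients with confirmed AMI are a real clinical population, and the Background names transmural or not, within AMI, as a question that bears on the choice of treatment. C's PPV and NPV are valid conditional on confirmed AMI, and its PPV is overstated only if carried over to all suspected patients.

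**Conclusion.** The point holds for comparison A. Computed within its two groups, PPV cannot be lower than the PPV for transmural AMI among suspected patients, and it is higher unless no non-transmural patient tests positive. That direction needs no assumption about the split or the positive rate.

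The size does. Over the grid above, the overstatement runs from 0.03 (120 transmural, 9% positive) to 0.47 (40 transmural, 50% positive), with 0.899 against 0.693 in the middle case. It also rests on the subset reading of the denominator and on accuracy exactly at the protocol's limit.

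The consequence is confined to the reported predictive values and to how A's results, including its LR+, are read as a test for transmural AMI. It is a worthwhile, inexpensive correction to reporting and does not challenge the study's objectives.

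**What to change.** - Do not report PPV and NPV within comparison A's two groups. Keep its sensitivity, specificity and likelihood ratios, which the primary objective needs.
- Compute PPV and NPV for transmural AMI, and for each class of the Table 3 score, over all included patients, and state that denominator.
- Add transmural versus all others as a companion to A, with sensitivity, specificity, likelihood ratios, PPV and NPV. This also shows what A's LR+ becomes once non-transmural patients are counted.
- Keep C's PPV and NPV, labelled as conditional on confirmed AMI.

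The cost is a few sentences in the analysis text and one extra table from data already planned. Patients, samples and selection rules stay as they are. The price is a PPV for transmural AMI that will probably look less favourable.
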